## Methods

### Design

#### Overview

This study is a case-controlled, prospective study consisting of two groups: one group of healthy control individuals who do not have symptoms of alcohol use disorders or anxiety and one experimental group that meets the selection criteria described in the Study Population and Setting section. Participants in both groups will be matched for age and sex, since both can be confounding factors regarding usage patterns of electronic devices. Both groups will receive mobile and wearable sensors that will track their physiological and behavioral activity over the course of 1 month. Both groups will also take the State-Trait Anxiety Inventory (STAI) [13], the Beck Depression Inventory-II (BDI-II) [14], and the Alcohol Use Disorders Identification Test (AUDIT) [15] once per week through the HumanITcare app downloaded on their phones. Participants will be instructed on the use of the app during the initial visit, along with receiving their wearable sensors (ie, Fitbits). The data will be monitored by the research team through an online, encrypted compilation of participants’ data.

The HumanITcare platform allows for the collection of data from the participants; the platform also provides a source of data for the researchers to verify that each participant’s data are being collected appropriately and that the Fitbit devices are working properly. The HumanITcare app that participants download to their phones collects data from the phones and sends them to the HumanITcare platform. As stated above, the app sends notifications to the participants once a week to remind them to complete the questionnaires. Also, it provides a *help* button so they can contact the researchers if needed (see the HumanITcare App section below).

#### Study Population and Setting

The study will be conducted at the Hospital Clínic de Barcelona and is a single-center national study. Experimental participants will be drawn from the outpatient clinic at the Addictions Unit of the Hospital Clínic de Barcelona, and control group participants will be drawn from random volunteers recruited through fliers and social media.

The research team members at the Hospital Clínic de Barcelona Addictions Unit will be tasked with finding eligible subjects for the experimental group. The inclusion criteria for the experimental group participants are as follows: must be between the ages of 18 and 70 years; must have knowledge and daily use of new technologies; must have an alcohol use disorder, based on the Diagnostic and Statistical Manual of Mental Disorders, 5th Edition (DSM-5) [16]; must have significant anxiety symptoms (STAI score >33rd percentile); and must have been informed about the study and signed the data processing consent form. Potential experimental group participants are not eligible if they meet any of the following criteria: their mobile device is not compatible with the Android mobile operating system (OS); they have a diagnosis of affective disorder, based on the DSM-5; they have cognitive deficits that prevent proper participation; or they actively consume other substances, in addition to alcohol, except nicotine.

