**Methods:**

We propose to conduct a study among a group of 60 participants split into two subgroups—experimental and control—of 30 participants each. The experimental group will be recruited by physicians from the Hospital Clínic de Barcelona, and the control group will be recruited on a volunteer basis through fliers and social media. All participants will go through pretraining to ensure technological capability and understanding of tasks, then each participant will download the HumanITcare app and will be given a wearable sensor (ie, Fitbit). Throughout the 4-month period, participants will be monitored on a range of factors, including sleep cycle, heart rate, movement patterns, and sociability. All data from the wearable sensors and the mobile devices will be saved and sent to the HumanITcare server. Participants will be asked to complete weekly questionnaires about anxiety, depression, and alcohol use disorder symptoms. Research assistants will ensure timely responses. The data from both sensors will then be compared to the questionnaire responses to determine how accurately the devices can predict the same symptoms.

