#### Recruitment

There will be a total of 60 participants split between the experimental and control subgroups (see Figure 1).The recruitment of the 30 experimental patients, conducted by psychiatrists and clinical psychologists, will take place in the outpatient clinic and day hospital of the Addictions Unit of the Hospital Clínic de Barcelona. The usual health care professionals for patients with anxiety symptoms will refer the selected patients to the research team who will assess whether the selected patients meet the eligibility criteria. The 30 healthy control participants will be recruited using brochures distributed by the Faculty of Medicine at the University of Barcelona, as well as through social media.

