#### Initial In-Person Visit: First Visit

Once deemed eligible by the research team, participants who meet the requirements for the experimental group, as well as the volunteer control participants, will be called to the Hospital Clínic de Barcelona. The first visit will last approximately one hour and will include an explanation of the project to the participants with time for them to ask questions and clarify any doubts. We will explain to the participants’ their rights and obtain their informed consent in the presence of the research team. We will also explain the measurement of the following variables: age, gender, education level, marital status, symptoms of anxiety (measured with the STAI), symptoms of depression (measured with the BDI-II), evaluation of alcohol use disorder (measured with the AUDIT), use of medication, medical comorbidities, and substance use. Those experiencing current medication or substance abuse will not be considered for the healthy control group.

Once the variables are profiled, each participant will be instructed to download the HumanITcare platform app and will receive their data encryption code and password. The app will use the participants’ mobile phone sensors to collect and consolidate data, which are then sent to the research team for evaluation. A Fitbit device will also be provided and each participant will be informed of their obligation to return the device once the study is completed. For proper operation of the Fitbit, participants will be instructed to access the Fitbit app through their personal email and to specify their age, sex, weight, height, and date of birth. This app complies with data protection laws.

Physiological and behavioral data from the participants’ smartphone devices will be compiled in the HumanITcare servers and will be transmitted, along with the data collected in the Fitbit servers, to a separate server available to the research team, which assigns each participant a unique, randomized character code that functions as a profile name (eg, mt1e45al). The data collected through the HumanITcare app and servers and the Fitbit servers for each participant will be represented by this 8-digit code in order to protect each participant’s privacy.

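### Controls labelled random are self-selected from a different source population than the cases, so sensor differences between the groups can partly reflect who was recruited

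*Protocol article*

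**What the plan says.** All references are to the Protocol article.

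- **Label for controls** (Study Population and Setting): "control group participants will be drawn from random volunteers recruited through fliers and social media".
- **Channels** (abstract, Methods): "the control group will be recruited on a volunteer basis through fliers and social media". The Recruitment section is more specific: controls are recruited "using brochures distributed by the Faculty of Medicine at the University of Barcelona, as well as through social media".
- **Source of cases** (Recruitment): recruitment "will take place in the outpatient clinic and day hospital of the Addictions Unit of the Hospital Clínic de Barcelona", with the patients' usual clinicians referring them to the research team.
- **Matching** (Design, Overview): "Participants in both groups will be matched for age and sex, since both can be confounding factors regarding usage patterns of electronic devices". No other matching factor is named.
- **Baseline data** (Initial In-Person Visit): the variables include "age, gender, education level, marital status". Employment, work schedule and income are not in the list.
- **Analysis** (Statistical Methods): mean, median, SD and range, for everyone and then for each group to allow a between-group comparison. No adjustment is stated.
- **Limitations** (Discussion): socioeconomic selection is conceded for the Android-only restriction. The difference in source between cases and controls is not mentioned.

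**The concern.** In the methods of a case-control study, the word random suggests that controls represent some defined population. Here they are people who chose to respond to a brochure or a post, and they come from a different pool than the clinician-referred patients. Apart from age and sex, nothing in the design makes the pools alike.

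The signals in Table 1 (sleep, steps, distance, phone use, calls and texts) are behavioural and can vary with education and social circumstances. The two-group sensor comparison is part of the primary objective. The primary outcome, how well an algorithm predicts symptoms, is exposed as well. If both groups are pooled, group membership goes with both the questionnaire scores and the recruitment source, so a model could look accurate partly because it recognises where a participant was recruited.

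**Working it through.** **1. The label against the channels.** The sentence that uses the word random also says that the controls are volunteers reached by fliers and social media. The abstract and the Recruitment section agree on volunteering. No sampling frame or random selection appears anywhere. The controls are self-selected on the article's own description, and this step needs no assumption.

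**2. The matching rationale.** Age and sex are matched because they may confound device-usage patterns. Education plausibly meets the same test. The Discussion accepts that socioeconomic status is linked both to phone type and to anxiety and depression. Neither education nor socioeconomic status is matched.

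**3. Possible size.** The article gives no figure to reproduce: no effect size, SD, alpha or power, and no education distribution. The inputs below are therefore assumptions, except the 30 per group.

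- Spurious difference (SD) = gap in share with higher education × effect of education on the sensor feature (SD).
- Standard error of a two-group difference = √(1/30 + 1/30) = √(2/30) = 0.258 SD, treating the groups as independent.
- Chance of a nominal two-sided 5% result with no disorder effect = Φ(d/0.258 − 1.96) + Φ(−d/0.258 − 1.96).

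| Gap | Effect (SD) | Spurious difference d (SD) | d / SE | Chance of a nominal 5% result |
|---|---|---|---|---|
| 0.20 | 0.3 | 0.06 | 0.23 | 5.6% |
| 0.20 | 0.8 | 0.16 | 0.62 | 9.5% |
| 0.40 | 0.5 | 0.20 | 0.77 | 12.1% |
| 0.60 | 0.3 | 0.18 | 0.70 | 10.7% |
| 0.60 | 0.8 | 0.48 | 1.86 | 46.0% |

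The low end is negligible and the high end is not. The article states no between-group test, so the standard error and the 5% level serve only as yardsticks.

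**4. Cost of adjusting for education.** With equal groups and education shares symmetric about 50%, the correlation r between group and education equals the gap. The standard error of the adjusted group difference rises by the factor 1/√(1 − r²), leaving aside any gain from explained residual variance.

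- 60% v 40% (r = 0.2): 1/√0.96 = 1.02, up 2%.
- 70% v 30% (r = 0.4): 1/√0.84 = 1.09, up 9%.
- 80% v 20% (r = 0.6): 1/√0.64 = 1.25, up 25%.
- 90% v 10% (r = 0.8): 1/√0.36 = 1.67, up 67%.

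The larger the confounding, the more the adjustment costs.

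**The case against.** - **Random is loose wording.** The same sentence names the channels, and no sampling claim is made. This stands in part. A reader might infer that the article claims a probability sample, and it does not. The word is still wrong and is easily corrected.
- **Group composition is not documented.** A reader might infer that the controls are students and staff and that the sensor differences will reflect university life. The documents do not support that. The brochures are distributed by the Faculty, but the article does not say to whom. Social media is a second channel. Age matching to cases aged 18 to 70 limits a student-heavy group, and cases must be daily users of technology. This stands: the claim is only that differences can partly reflect source population.
- **Covariates belong in an analysis plan.** An unseen plan may adjust for education, and its absence from a condensed article is not a fault. This stands. But such a plan cannot change the label, the recruitment channels or the matching factors.
- **The raw group contrast is not the primary outcome.** This is true, but a pooled prediction model is open to the same confounding.
- **Nothing can be changed now.** Recruitment ended in November 2019 and data collection in December 2019, so controls can no longer be chosen by education. Data were still being processed at publication, so the wording and the analysis could still change.
- **It is a pilot.** This lowers the stakes but does not remove the need to name the limitation.

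**Conclusion.** The point holds in a limited form. The controls are self-selected, they come from a different source than the cases, and they are matched on age and sex only. The comparison that the article states is unadjusted. Sensor differences, and any sensor-symptom model fitted to both groups together, can therefore partly reflect source population and not disorder, and the Discussion does not concede this.

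Neither the direction nor the size is known. The range of 0.06 to 0.48 SD against a standard error of 0.26 SD rests wholly on assumed education gaps (20 to 60 points) and assumed education effects (0.3 to 0.8 SD). It shows that the bias could be anything from trivial to nearly two standard errors, and it does not show that a bias is present.

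**What to change.** 1. In Study Population and Setting, drop the word random and describe the controls as self-selected volunteers recruited through a medical faculty and social media.
2. Report education and marital status by group.
3. Report the between-group sensor comparison adjusted for education beside the unadjusted one.
4. Report sensor-score associations within each group as well as pooled.
5. In the Discussion, name the control source as a limitation next to the one on Android phones.

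**Cost.** Items 1 and 5 are wording, and items 2 to 4 use data already listed for collection. The adjusted intervals will be wider: slightly if education is roughly balanced, substantially if it is not (standard error up about 67% at 90% v 10%). Within-group associations rest on about 30 participants each. Confounding by employment or daily routine would remain, because neither is listed as recorded. Selecting controls on education, and recording employment, are options only for a follow-up study.

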### Study Objectives

Due to emerging research on digital biomarkers and the accuracy of passive monitoring of data in patients with mental health disorders, we propose to conduct the REMOTE Study among a group of 60 participants split into two subgroups of 30 participants each This study will be conducted in the Addictions Unit at the Hospital Clínic de Barcelona. The primary objective of this study is to analyze the digital physiological patterns of two groups of participants—one group with symptoms of anxiety disorder and alcohol use disorder and one healthy control group without these disorders—using data collected from a mobile device (ie, smartphone) and a wearable sensor (ie, Fitbit). The data will be collected from the sensors through the HumanITcare platform. The data will then be compared with the symptoms validated in clinical questionnaires, which participants will complete four times over the course of the study, in order to determine whether the use of sensor data is an efficient and accurate means of presenting objective diagnoses rather than the subjective diagnoses of the status quo.

The secondary objective of this study is to analyze usability and patient satisfaction with the data collection service provided by the app and to explore the feasibility of this approach in clinical practice.

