**Questionnaire data: to be tested against estimation algorithm**		
	Self-reported anxiety symptoms	Assessed via the State-Trait Anxiety Inventory (STAI); participants receive STAI scores ranging from 0 (lowest number of symptoms) to 60 (greatest number of symptoms), which are then transformed into percentiles according to age and sex
	Self-reported depression symptoms	Assessed via the Beck Depression Inventory-II (BDI-II); participants receive BDI-II scores ranging from 1 to 63: a score of 0-13 indicates minimal depression, 14-19 indicates mild depression, 20-28 indicates moderate depression, and 29-63 indicates severe depression
	Self-reported alcohol use symptoms	Assessed via the Alcohol Use Disorders Identification Test (AUDIT); participants receive AUDIT scores ranging from 0 to 40: a score of ≥8 is associated with harmful or hazardous drinking and a score of ≥13 in women or ≥15 in men is likely to indicate alcohol dependence

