## Discussion

The study is focused on patients diagnosed with anxiety and alcohol use disorder, but participants are also monitored for depressive symptoms throughout the trial, although these were not part of the initial inclusion criteria. Including this data while interpreting results could be a potential confounding factor. However, we would like to emphasize that while we recognize that anxiety disorders and depressive disorders are not clinically synonymous, major studies strongly support the finding that there are high rates of comorbidity between the two. In one study, results showed that 67% of patients with a depressive disorder also had a current anxiety disorder and 75% had a lifetime anxiety disorder [19]. Harvard researchers Jukka-Pekka Onnela and John Torous conducted a similar study using participants diagnosed with major depressive disorder and reported “Patients in this study were not excluded due to comorbidity of additional illnesses,” such as anxiety [6]. Due to this evidence, we believe there is justification for using participants who have symptoms of both. To avoid confusion, future research should prescreen for anxiety as well as depression, and standardize the initial sample. Researchers may also decide to use anxiety and depression interrelated questionnaires, such as the Depression Anxiety Stress Scales (DASS), that take into account the comorbidity of the two disorders, rather than primarily depression-related (ie, the BDI-II) or primarily anxiety-related (ie, the STAI) surveys, in order to improve reliability and validity of patient measures.

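### The case rule calls STAI above the 33rd age-sex percentile significant anxiety, a level about two-thirds of the norm population exceeds, and no stated score applies the symptom-free description of controls

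*Protocol article*

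**What the plan says.** Under Study Population and Setting, a case needs a DSM-5 alcohol use disorder and "must have significant anxiety symptoms (STAI score >33rd percentile"). Table 1 says that STAI scores run from 0 to 60, "which are then transformed into percentiles according to age and sex". The entry criteria ask for no anxiety diagnosis, yet the Discussion states "The study is focused on patients diagnosed with anxiety and alcohol use disorder", and the abstract's Conclusions describe the cases in the same terms.

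Controls are defined in words. The Design Overview has "one group of healthy control individuals who do not have symptoms of alcohol use disorders or anxiety", and Study Objectives has "one healthy control group without these disorders". They are volunteers recruited through fliers and social media. The First Visit section adds an exclusion: "Those experiencing current medication or substance abuse will not be considered for the healthy control group". STAI, BDI-II and AUDIT are among the variables at that visit for both groups. Table 1 prints AUDIT cut-offs (8 or more for harmful or hazardous drinking), but as scoring guidance and not as eligibility limits.

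**The concern.** A percentile cut fixes the share of the norm population that passes it. A cut at the 33rd passes most people, some of them less anxious than the median for their age and sex. Such a rule does not select significant anxiety, and it is not a diagnosis. Conclusions about patients diagnosed with anxiety would describe a population that the entry rule does not define.

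The control side adds to this. The two descriptions differ: someone with mild symptoms and no disorder satisfies Study Objectives but not the Design Overview. No score is given that would settle such a case. Read against the case rule, having no anxiety symptoms could mean a score at or below the 33rd percentile, or something looser that overlaps with the cases.

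At stake is the comparison of the two groups' digital patterns named in the primary objective. All cases have alcohol use disorder, while their anxiety has only a low floor. A difference in sensor patterns driven mainly by alcohol use disorder could be reported as an anxiety phenotype.

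**Working it through.** The article gives no sample-size or power calculation, so there is no figure of its own to reproduce. The check works from the printed cut.

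**Inputs**
- Case cut: 33rd percentile (Study Population and Setting).
- Scale: age- and sex-specific percentiles (Table 1).
- Group size: 30 per group (Study Objectives).

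**Step 1. Share of the reference population above the cut (no distributional assumption)**
- 1 − 0.33 = 0.67.
- Share between the cut and the median: 0.50 − 0.33 = 0.17. Of those who pass, 0.17 / 0.67 = 25% are below the median.

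**Step 2. Label against criterion**

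| Section | Description of anxiety in cases |
|---|---|
| Study Population and Setting | significant symptoms, meaning STAI above the 33rd percentile |
| Study Objectives | symptoms of an anxiety disorder |
| Discussion and abstract Conclusions | diagnosed |

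Only the first row is a rule that can be applied, and it supports neither its own adjective nor the last row.

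**Step 3. How much the reading of the control definition matters (illustration)**

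Assume that STAI is normal in the norm population, that cases are that population truncated at the cut, and that controls also come from it.
- z(0.33) = −0.440; the normal density there is φ = 0.362.
- Case mean: φ / 0.67 = +0.54 SD.
- Unscreened controls: mean 0, so the gap is 0.54 SD.
- Controls at or below the 33rd percentile: mean −φ / 0.33 = −1.10 SD, so the gap is 0.54 + 1.10 = 1.64 SD.
- Ratio of the two gaps: 1.64 / 0.54 = about 3.

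For unscreened controls:
- Expected number meeting the case anxiety criterion: 30 × 0.67 = 20.1, or about 20 of 30.
- Probability that at least 15 of 30 do (binomial, p = 0.67): 0.98.
- Probability that a random case scores above a random control: the mean case percentile, (0.33 + 1) / 2 = 0.665.

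Even here the expected gap is above zero. With controls held at or below the cut, the groups do not overlap on STAI at entry.

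**The case against.** The strongest reply concerns the controls. The article does restrict them: they are to have neither symptoms nor the disorders, and current substance abuse excludes them. It condenses a full protocol that is not shown, and the recruitment figure is missing, so a numerical control limit may exist. That stands. A reader might infer that controls are unscreened, or that the two groups do not differ in anxiety. The documents support neither inference. Nothing says that a control at the 50th percentile would be accepted as symptom-free.

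The 20-of-30 and 0.54 SD figures also do not describe the actual sample. Cases are Addictions Unit patients, and the Recruitment section has them referred by professionals who care for patients with anxiety symptoms, so their scores may lie well above the minimum that the rule allows. This stands too, and it is why the figures serve only as illustrations.

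Third, the primary outcome estimates questionnaire scores from sensor data. It uses each participant's own score, and a spread of scores in both groups does not bias it. No case-control discrimination statistic is stated. So the effect falls on the group comparison in the primary objective and Statistical Methods, and on what may be claimed about the case population.

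Finally, the study calls itself a feasibility pilot. That lowers the stakes but does not reconcile the printed number with its label, or the word *diagnosed* with the entry rule.

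**Conclusion.** The point holds for the case definition. As printed, the anxiety criterion passes about 67% of the reference population, and a quarter of those who pass are below the median. This follows from the definition of a percentile and depends only on which norms are used. The article does not name them, and ordinary population norms are assumed here. The criterion contradicts its label, and calling the cases diagnosed with anxiety goes beyond the entry rule.

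For the controls a narrower statement holds. The article gives a verbal restriction and no score that applies it, so separation on anxiety is not guaranteed. It is not shown to be absent. Under the assumptions of Step 3, the two readings of the restriction give criterion-driven gaps of 0.54 and 1.64 SD; neither estimates the gap in the recruited sample. The alcohol contrast is better secured, by the DSM-5 requirement in cases and the substance-abuse exclusion in controls. That is why a group difference could reflect alcohol use disorder rather than anxiety.

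**What to change.** 1. Verify the printed percentile against the full protocol and correct it if it is an error.
2. If it is right, replace *significant* and *diagnosed* with a description such as alcohol use disorder with STAI above the 33rd age-sex percentile, and limit the conclusions to that population.
3. State how the symptom-free description of controls was applied, and reconcile the wording of Study Objectives with that of the Design Overview.
4. Report baseline STAI and AUDIT in both groups against the same cut-offs: the case STAI cut and the article's AUDIT value of 8 or more.
5. Repeat the group comparison without controls who exceed either cut, as a sensitivity analysis.

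Do not add a restriction of cases to a high STAI percentile, such as the 75th. No such cut has a source in the article, and contrasting extreme groups tends to inflate apparent accuracy.

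The cost is some rewording and one analysis on first-visit scores. Data collection ended in December 2019, so entry cannot be changed, but reporting can. The downside is a smaller control set in that one analysis, whose age and sex balance with the cases should be rechecked.
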